### Data Management Plan

Source data will include participant demographic data, consent, assessment data logged by participants and the research or study team on the REDCap system, as well as any other supplementary data logged by the research or study team. Source data will also include participant interview transcripts. Access to the research data will be limited to assigned trial staff and researchers to allow trial-related monitoring and audits and ensure compliance with data management regulations. All data will be stored on secure University of Nottingham platforms, that is, in access-restricted, password-protected online research folders on the University of Nottingham OneDrive (Microsoft Corporation). Access will be restricted by user identifiers and passwords (encrypted using a 1-way encryption method). Research data will be anonymized by allocating a unique trial-specific number or code in the database. It will be ensured that identifiable data will be stored separately from research data and that the researchers do not have access to the identifiable or randomization data to retain blinding.

### Interview Data and the Use of Videoconferencing

Only platforms approved by the University of Nottingham (ie, Microsoft Teams) will be used for conducting interviews, as these platforms are encrypted. To retain privacy and confidentiality, researchers will ensure that they are working in an area where conversations cannot be overheard and the computer screen cannot be observed. Researchers will not use personal accounts or devices to contact participants. Interviews will be recorded on Microsoft Teams to facilitate transcription; interview recordings will be deleted from Microsoft Teams as soon as they are transcribed. The interview recordings will be pseudonymized, and any identifying information will be redacted in transcripts. Interview recordings and transcripts will be saved on access-restricted, password-protected online research folders on the University of Nottingham OneDrive.

The trial will follow the electronic data management policy and procedures of the University of Nottingham (sponsor) in accordance with the Data Protection Act 2018.

### Analyses

#### Statistical Method

All analyses will be conducted on an ITT basis; a description of the planned ITT and sensitivity analyses for both primary and secondary outcomes conforming to the estimand framework [36] has been provided in Multimedia Appendix 2. After exploratory analysis, multilevel modeling will be implemented to quantify the treatment effect estimate and its precision over the follow-up time points, with the treatment implementation group and each participant as a higher-level analytic unit and baseline measure, allocation status, follow-up time point, and interaction of follow-up×allocation as covariates with fixed effects. A similar analytic approach will be used to quantify the treatment effects on all secondary outcomes. Missing values will be explored and imputed using a multiple imputation approach under the missing at random assumption for the missingness mechanism [37]. Sensitivity analyses will be performed to explore the robustness of the treatment effect estimate, sensitive to the influence of data missingness, various limitations of the data, assumptions, and analytic approaches to data analysis. The latest available version of Stata (StataCorp) will be used for data analysis. A detailed trial statistical analysis plan setting out the proposed analyses has been published [38].

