### Sample Size

With reference to the trial’s primary outcome, 5 points on the PSS-14 will be considered as the minimum clinically important difference. Assuming a 2-tailed .05 significance level with 90% power (using analysis of covariance) and SD 7.7, a baseline and follow-up correlation of 0.2, and the correlation among follow-up measures of 0.7, a total of 76 participants will be needed to estimate the treatment effect from baseline at 20 weeks after randomization. Assuming the average group size is 8, the intraclass correlation coefficient is 15%, and the attrition rate is 25% (considering potential loss to follow-up), the final sample size was inflated to 208 participants to be randomly recruited in 26 groups (1:1 ratio) across all the recruitment sites. However, upon monitoring follow-up rates after approximately one-third of the participants were randomized, it was highlighted by a blinded independent statistician that the follow-up rate was approximately 62% and the group size was approximately 10. Therefore, the trial management group decided to update the sample size with 85% power to mitigate the loss to follow-up. A substantial amendment was submitted, and ethics approval was received for the sample size to be increased to 260 participants, divided across 26 groups.

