### Randomization and Blinding

Once consent is obtained on the REDCap platform, they will be randomly allocated in a 1:1 ratio to either the MBCT-L or SRP intervention. The online format and delivery of the interventions allow the allocation of participants to take place across the participating sites; this is expected to facilitate timely and sufficient recruitment within and across the intervention groups running at any site until the 2 intervention groups are full in each recruitment wave throughout the trial. Randomization will be conducted via a web-based randomization system set up by a clinical decision support system supported by the University of Nottingham. The randomization system will ensure that all the researchers involved in the outcome assessments ([name]) remain blinded to intervention allocation. Participant allocation to either intervention arm will be solely facilitated by a project administrator who will manage the randomization system independently of the research team following specified standard operating procedures. The study statistician will also be blinded to treatment allocation. In the event of inadvertent unblinding, the details of the unblinding incident will be recorded in the study log, relevant sponsor and monitoring committees will be informed (eg, the university sponsor, the research ethics committee, and the ARC-EM Scientific Committee), and the extent and impact of the unblinding will be assessed. All participants will complete the same outcome measures in the survey, so that researchers or outcome assessors will not be able to determine the participant’s group based on the response. In view of the nature of the interventions, participants cannot be blinded; they will be informed of which treatment arm they have been randomized to and will be notified through a letter or via email sent to them by the project administrator, which will also include information on the intervention delivery (eg, dates and times, requirements for attendance, and joining instructions).

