### Interventions

#### Overview

The 2 interventions that participants will be randomized, MBCT-L or SRP, will be delivered online via a videoconferencing platform, that is, Microsoft Teams, taking place in a group format once a week at different times and days, allowing participants to indicate (at the time of consent) which group times they would opt for if they were to be randomized to either intervention. The sessions on either intervention will not be recorded. There will be 3 recruitment waves in total, with the interventions starting at various time points during a given recruitment wave and both intervention arms starting in the same week in each recruitment wave to allow synchronized data collection. The CONSORT (Consolidated Standards of Reporting Trials) flowchart (Figure 1) depicts an outline of recruitment, consent, randomization, and assessment processes.

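### The stated primary model leaves out recruitment wave, although both arms run in parallel within 3 waves; if outcomes differ between waves, the standard error will be somewhat too large

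*Protocol article*

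**What the plan says.** The Statistical Method section describes a multilevel model "with the treatment implementation group and each participant as a higher-level analytic unit" and lists its fixed effects as "baseline measure, allocation status, follow-up time point, and interaction of follow-up×allocation as covariates with fixed effects". That is the whole of the stated model. For further detail the section points to a published statistical analysis plan and an estimand appendix, neither of which is at hand.

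The design sections describe wave as part of how the trial is run. Interventions, Overview: "There will be 3 recruitment waves in total", with "both intervention arms starting in the same week in each recruitment wave to allow synchronized data collection". Randomization and Blinding: "they will be randomly allocated in a 1:1 ratio to either the MBCT-L or SRP intervention", with recruitment into the groups continuing "until the 2 intervention groups are full in each recruitment wave throughout the trial". Nothing states that allocation is stratified by wave, and no between-wave variance is given.

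**The concern.** Because both arms are filled and started side by side in each wave, anything that moves stress scores for a whole wave moves both arms and drops out of the treatment contrast. A model without wave does not know this. It sees groups in one wave scoring higher than groups in another, puts that into the group-level variance, and charges it to the standard error of the arm effect.

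A wave difference is plausible, though not documented. Recruitment ran from 29 August 2023 to 30 April 2024 and follow-up ended on 30 September 2024, so the 20-week scores fall at different times of year. The sample-size section assumes a baseline to follow-up correlation of only 0.2. This suggests that baseline PSS-14 would absorb little of such a shift, although it is a correlation between individuals, not between waves.

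What is at stake is precision. The trial assumes an intraclass correlation of 15%, has 26 groups, saw about 62% follow-up, and lowered its power target from 90% to 85%.

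**Working it through.** **Inputs from Sample Size.** Difference 5 points ("5 points on the PSS-14 will be considered as the minimum clinically important difference"); SD 7.7, two-sided 5%; correlations 0.2 (baseline to follow-up) and 0.7 (among follow-ups); ICC 0.15; after the amendment, 26 groups of about 10, 62% followed and 85% power.

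**The plan's own figures reproduce.**
- Variance factor for ANCOVA on three follow-ups: (1 + 2×0.7)/3 − 0.2² = 0.76.
- 90% power: 2×(7.7×3.242/5)²×0.76 = 37.9, so 38 per arm and 76 in total. 76×(1 + 7×0.15) = 155.8, and 155.8/0.75 gives 208.
- 85% power: 33 per arm, 66 in total. 66×(1 + 9×0.15) = 155.1, and 155.1/0.62 = 250.2, which rounds up to 26 groups of 10, or 260. The article does not show this last step; it is the route that fits.

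**Assumptions added here.** 13 groups per arm, spread over the waves as 5, 4 and 4; 0.62×10 = 6.2 completers per group; tests on 26 − 2 = 24 group-level degrees of freedom without wave and 22 with it; a share w of total variance due to wave, taken from within the 0.15.

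**Closed form.** In units of total variance, a group mean has variance (0.15 − w) + 0.85/6.2 = (0.15 − w) + 0.1371 once wave is removed. With the arms balanced within waves, this is what truly governs the contrast. Without a wave term, the model adds c×w:
- wave effects drawn at random: c = (13 − 57/13)/12 = 0.718, where 57 = 5² + 4² + 4²;
- wave effects scaled to exactly the stated share: c = 1, or 13/12 when the divisor is the 12 degrees of freedom per arm.

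| w | with wave | without wave (c = 0.718 / 1 / 13/12) | SE excess |
|---|---|---|---|
| 0 | 0.2871 | 0.2871 | 0% |
| 0.02 | 0.2671 | 0.2815 / 0.2871 / 0.2888 | 2.7% / 3.7% / 4.0% |
| 0.05 | 0.2371 | 0.2730 / 0.2871 / 0.2913 | 7.3% / 10.0% / 10.8% |

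The SE excess is the square root of the variance ratio, minus 1. It does not depend on the SD or on the variance factor.

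**Level of the SE.** SE = √(2/13 × 7.7² × factor × group-mean variance). At w = 0 this is 1.41 with factor 0.76, 1.59 with factor 1 − 0.2² = 0.96 (ANCOVA on one follow-up), and 1.62 with factor 1. The primary endpoint is the single 20-week score, so about 1.6 suits it better than 1.41, which averages three follow-ups.

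**Simulated power for 5 points and type I error.**

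| w | power without → with wave, SE near 1.6 | power without → with wave, factor 0.76 | type I error without wave |
|---|---|---|---|
| 0 | 84.8% → 83.9% | 92.6% → 92.4% | about 5% |
| 0.02 | 85.3% → 86.8% | 93.2% → 93.9% | 4.6% (factor 0.76) |
| 0.05 | 86% → 90% | 94.9% → 96.2% | 3.2% (SE near 1.6); 3.9% (factor 0.76) |

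The first power column used 3,000 runs per setting and REML. The second used 20,000 runs on group means, with waves of 4, 4 and 5 groups per arm. To the nearest half point, the changes are −1 to 0, +0.5 to +1.5 and +1.5 to +4. In the second set, the actual spread of the treatment estimate was the same with and without wave (1.369 at w = 0.02, 1.281 at w = 0.05). Only the reported SE differs, and with wave in the model type I error stays at about 5%.

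**The case against.** The strongest reply is that this is an optional efficiency covariate in a condensed article. The analysis plan is published and may already contain wave, and the Statistical Method section foresees sensitivity analyses on alternative analytic approaches. That is fair as to weight. But the article does not leave the model open: it lists the covariates and the levels, and wave is in neither list.

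Three stronger readings are tempting, and the documents support none of them.

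- A reader might infer that the standard error *is* too large. That holds only if outcomes differ between waves after baseline adjustment, and no figure or statement shows that they do. With no wave effect there is no excess, and adding wave costs a little power.
- A reader might infer that the analysis breaks a stratified randomization. Stratification by wave is nowhere stated; the balance assumed here follows from parallel filling to a 1:1 ratio.
- A reader might infer a biased estimate or too many false positives. With arms balanced within waves the estimate is unbiased, and the error runs the other way, towards a conservative test.

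Two further points stand. The Interventions overview also says that starts are spread over time within a wave, so a 3-level term may catch only part of a seasonal shift, and the figures above are then upper values for a given seasonal share. The article also names no degrees-of-freedom method; the 24 and 22 used here are assumptions.

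**Conclusion.** The point holds as a conditional, minor one. The stated primary model omits a feature of the design within which the arms run in parallel. If that feature carries outcome variance, the interval for the treatment effect will be wider than it need be. At assumed wave shares of 2% and 5% of total variance the excess in the SE is about 3-4% and 7-11%; at 5%, type I error falls to about 3-4%. If wave carries nothing, leaving it out does no harm. The result rests on the assumed wave share, near-equal numbers of groups per arm within each wave, 6.2 completers per group and the assumed degrees of freedom. It calls for a cheap improvement and is no threat to the trial's validity.

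**What to change.** Add recruitment wave (3 levels) as a fixed effect to the primary model and to the matching models for the secondary outcomes. Wave can be derived from the randomization date, so no new data are needed. The cost is 2 of about 24 group-level degrees of freedom, which is under 1 point of power if wave has no effect (0.2 to 0.9 in the runs above).

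Timing matters. The abstract says that follow-up is complete and analysis underway. If the primary model is already locked, keep it and report the wave-adjusted model as a sensitivity analysis, labelled with the date on which it was specified. If the analysis plan already contains wave, bring the article's covariate list into line with it.

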#### Economic Analysis

The initial estimates of cost-effectiveness will require a base case analysis before exploring the impact of uncertainty. To perform the base case analysis, first, each individual participant within the trial will have an estimated intervention cost, a health care cost, a QALY score based upon their EQ-5D-5L responses, and a PSS-14 score. Second, using ordinary least squares regression, incremental costs, QALYs, and PSS-14 scores will be estimated for MBCT-L versus SRP groups. These incremental values will then be used to estimate the ICER per QALY gained and the ICER per PSS-14 reduced. The base case analysis will use data from all participants who report complete data; however, a secondary analysis using all participants’ data will be conducted, with missing data controlled for using multiple imputation [37].

The base case analysis will not include any productivity costs (ie, due to absence from work), as per NICE guidelines [39]. A secondary analysis will be conducted, whereby productivity costs will also be included, using a similar approach as the base case analysis. All analyses will be conducted using the latest version of Stata. Multimedia Appendix 3 provides a detailed economic analysis plan.

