#### Measures of Cost-Effectiveness

The primary measure of cost-effectiveness includes the incremental cost-effectiveness ratio (ICER) per quality-adjusted life year (QALY) gained for the MBCT-L versus SRP interventions.

Secondary measures include ICER per reduction in PSS-14 scores for MBCT-L versus SRP.

The following outcome data will be collected:

Health-related quality of life outcomes will be collected at baseline and 6, 12, and 20 weeks after randomization. These will be measured via the widely used EQ-5D-5L [34].A health economics assessment adapted from the Client Service Receipt Inventory [35], which has been successfully used in a wide variety of studies of mental health, community-based health, and social care services, will be conducted. A mental health customized version will be administered to collect self-reported resource use for 6 months preceding data collection at baseline, 6 weeks preceding data collection at 6-week follow-up, 6 weeks preceding data collection at 12-week follow-up, and 8 weeks preceding data collection at 20-week follow-up. It is intended that the data gathered from these measures will be used for a cost-effectiveness analysis, subject to trial outcomes, should MBCT be superior to SRP.

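### The base-case cost-effectiveness analysis is restricted to complete cases, which would drop at least about 38% of randomized participants at the interim follow-up rate; the planned imputed analysis should be the base case

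*Protocol article*

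**What the plan says.** All references are to the protocol article.

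- **Economic Analysis**, base case: "The base case analysis will use data from all participants who report complete data". The same sentence adds that "a secondary analysis using all participants’ data will be conducted, with missing data controlled for using multiple imputation". The section opens by saying that "each individual participant within the trial will have an estimated intervention cost, a health care cost, a QALY score", along with a PSS-14 score. Incremental values are to come from ordinary least squares regression, for which the article names no covariates.
- **Measures of Cost-Effectiveness**: "The primary measure of cost-effectiveness includes the incremental cost-effectiveness ratio (ICER) per quality-adjusted life year (QALY) gained". On the utility data: "Health-related quality of life outcomes will be collected at baseline and 6, 12, and 20 weeks after randomization". Resource use is recalled over the 6 weeks before the 6-week survey, then "6 weeks preceding data collection at 12-week follow-up, and 8 weeks preceding data collection at 20-week follow-up".
- **Statistical Method**: "All analyses will be conducted on an ITT basis". The sentence goes on to the primary and secondary outcomes and points to the estimand appendix. Missing values are to be multiply imputed under missing at random.
- **Sample Size**: after about one-third of participants had been randomized, an independent blinded statistician reported that "the follow-up rate was approximately 62% and the group size was approximately 10". The target was then raised to 260 in 26 groups.

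**The concern.** The trial knew during recruitment that follow-up was well below plan and enlarged the sample for that reason. The economic base case nevertheless uses only participants with nothing missing. The three resource-use windows (6 + 6 + 8 weeks) join end to end to cover the 20 weeks, and the EQ-5D-5L is taken at the same visits. A complete 20-week cost and QALY therefore calls for all three follow-up surveys, and someone who returned two of them would contribute nothing.

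Three things are at stake.

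1. **Bias.** Complete-case regression is biased if, given the covariates in the model, completion still depends on costs or quality of life. Staff who are more stressed, busier or less engaged may plausibly return fewer surveys.
2. **Lost information.** Partial follow-up data are discarded, although imputation could use them.
3. **Mismatch.** The clinical effect is to be estimated with multiple imputation, while the headline ICER would describe completers only. For the ICER per PSS-14 point, the same scale would be analysed in two different sets of participants.

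**Working it through.** **Inputs.** From Sample Size: N = 260, 26 groups, interim follow-up 62%, group size about 10, ICC 0.15, difference 5, SD 7.7, correlations 0.2 (baseline with follow-up) and 0.7 (among follow-ups), 85% power in the revision. From Measures of Cost-Effectiveness: three follow-up surveys. Applying 62% to each survey is an assumption, because the article gives a single rate and no visit.

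**Step 1: is 62% the rate the trial plans on?** Reproduce the sample sizes with a repeated-measures ANCOVA over three follow-ups.

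- Variance factor: (1 + 2 × 0.7)/3 − 0.2² = 0.76.
- Per arm: 2 × [7.7 × (z₀.₉₇₅ + z_power)/5]² × 0.76.
- 90% power: 37.9, so 38 per arm and 76 in total, as stated. Inflated: 76 × (1 + 7 × 0.15)/0.75 = 207.7, so 208, as stated.
- 85% power: 32.4, so 33 per arm and 66 in total. Inflated: 66 × (1 + 9 × 0.15)/0.62 = 250.2, which is 25.02 groups of 10. Rounding up to whole groups gives 26 groups and 260, as stated.

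The revised target is thus consistent with 62% follow-up. It is the trial's own planning figure.

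**Step 2: complete cases among 260, assuming 62% at each of three surveys.**

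| Assumption about who misses surveys | Share complete | Complete | Excluded |
|---|---|---|---|
| Same people miss every survey | 0.62 | 161 | 99 |
| Latent correlation 0.9 | 0.52 | 134 | 126 |
| Latent correlation 0.7 | 0.43 | 113 | 147 |
| Latent correlation 0.5 | 0.37 | 97 | 163 |
| Independent across surveys | 0.62³ = 0.238 | 62 | 198 |

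The first row is the most favourable case: the share complete at every survey cannot exceed the share complete at one. Exclusion is therefore at least 99/260 = 38%, before any missing items within a returned survey. The middle rows use a normal threshold model with a common correlation between visits; these correlations are illustrative and do not come from the article.

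**Step 3: if follow-up recovered to the 75% first planned.** The range is 0.75 × 260 = 195 down to 0.75³ × 260 = 110. At least 65 participants (25%) would still be excluded.

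**Step 4: the alternative.** The planned imputed analysis uses all 260.

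**The case against.** Several points on the other side have force.

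- **The imputed analysis is already planned.** Both results will exist, so the dispute is over which one is labelled the base case. This limits the harm. The label still decides the headline ICER, and the article does not say which result prevails if the two disagree.
- **A reader might infer that the ICER rests on a minority of participants.** The article does not show this. At 62% with the same non-responders throughout, 161 of 260 is a majority. Falling below half would require that fewer than 81% of those followed up (130/161) have complete data. That is plausible with three surveys, but no figure in the article establishes it.
- **The 62% is an interim rate** from about the first third of participants, at an unnamed visit. It is neither the final rate nor the completeness of the economic data, so every count above is conditional on it.
- **A reader might infer a flat contradiction with intention-to-treat.** The sentence sits under Statistical Method and continues to the primary and secondary outcomes, while the economic analysis has its own section and appendix. Nothing there departs from analysis by allocated arm. What remains is a loose fit with the literal word *all* and with the promise of values for each participant.
- **Complete-case regression does not strictly require data missing completely at random.** It is also valid if, given the model covariates, missingness is unrelated to the outcome. Completion that differs only by arm, for instance because the programmes differ in length, would not by itself cause bias, since arm is in the model. Bias is a risk here and has not been demonstrated; its direction is unknown.
- **The economic plan in Multimedia Appendix 3 is not shown.** It may define complete data and list covariates. That is why the absence of those details is not criticized here. The choice of base case itself is stated in the article.
- **The economic evaluation is not the primary objective**, and the article makes the cost-effectiveness analysis conditional on MBCT proving superior. The primary clinical inference is unaffected.

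**Conclusion.** The concern holds in a limited form. Taking complete cases as the base case is a stated choice and the weaker of two analyses already planned, in a trial that had seen low follow-up. If about 62% held at each survey, at least 99 of 260 randomized participants (38%) would leave the primary ICER. The assumed range of complete cases is 62 to 161 (24% to 62%), depending on how far the same people miss successive surveys. The size of any bias in the ICER cannot be derived from the article. What is established is a substantial exclusion, discarded partial data, and a headline economic result for a different set of participants from the clinical result.

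**What to change.** 1. Make the multiply imputed analysis of all randomized participants, by allocated arm, the base case, and report the complete-case analysis as a sensitivity analysis. This also matches the missing-at-random imputation planned for the clinical outcomes.
2. State whether the intention-to-treat sentence under Statistical Method covers the economic analysis or only the clinical outcomes.

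**Cost.** Both analyses are already planned, so no new data or methods are needed. Data collection has ended, however, and the base case has been published, so this is more than an edit: it needs a dated, justified change made before unblinded economic results are seen. If that is no longer possible, report both analyses with equal prominence, give the number of complete cases by arm, and keep the published label visible.
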